### 3.0 STUDY DESIGN

This phase I trial is designed to evaluate the safety and immunogenicity of LC002 for the treatment of individuals with chronic HIV-1 infection and HAART-induced durable suppression of viral replication. The study population will include HIV-infected men and women 18 to 50 years of age with a peak plasma HIV-1 RNA > 1000 copies/mL before initiation of HAART. Eligible subjects must have been and remain on a stable HAART regimen (containing drugs of at least two different classes) without changes or interruptions within the 24 weeks prior to study entry and must have a plasma HIV-1 RNA level < 50 copies/mL at least twice within 12 weeks prior to study entry. Subjects should have a CD4+ cell count > 300 cells/mm^3 at the time of entry and a nadir CD4+ cell count > 250 cells/mm^3.

Subjects in cohort 1 will be enrolled to receive one low-dose DermaVir vaccinations (3 subjects). Further enrollment of subjects into the medium and high dose cohorts 2 and 3 (3 subjects, respectively) will begin only after the safety data for cohorts 1 and 2, respectively, are available, and the criteria for enrolling into the next cohort are met (see section 9.1.3). The main criterion to start enrolling the next dose cohort will be the absence of a dose-limiting toxicity in any of the DermaVir subjects in the prior cohort. The actual immunization will be administered once, and after the four-week treatment phase and evaluations, subjects will be followed for an additional 48 weeks for safety.

Subjects will be sequentially enrolled into each cohort:

- Cohort 1:
  - Three subjects will receive a single low-dose vaccination (0.1 mg DNA/subject, 0.8 mL total, administered over two skin sites of 80 cm^2 each, 0.4 mL/site) at study day 0.
- Cohort 2:
  - Three subjects will receive a medium-dose vaccination (0.4 mg DNA/subject, 3.2 mL total, administered over four skin sites of 80 cm^2 each, 0.8 mL/site) at study day 0
- Cohort 3:
  - Three subjects will receive a high-dose vaccination (0.8 mg DNA/subject, 6.4 mL total, administered over eight skin sites of 80 cm^2 each, 0.8 mL/site) at study day 0.

## 4.0 SELECTION AND ENROLLMENT OF SUBJECTS

### 4.1 Inclusion Criteria

- 4.1.1 Ability and willingness of subject or legal guardian/representative to give written informed consent.
- 4.1.2 HIV-1 infection, as documented by any licensed ELISA test kit and confirmed by Western blot, HIV-1 culture, HIV-1 antigen, plasma HIV-1 RNA, or a second antibody test by a method other than ELISA is acceptable as an alternative confirmatory test at any time prior to study entry.
- 4.1.3 On a stable antiretroviral regimen (containing drugs of at least two different classes) without changes or interruptions for at least 24 weeks prior to study entry.
- 4.1.4 Plasma HIV-1 RNA level of less than 50 copies/mL, while on a stable antiretroviral regimen, obtained at least twice within the 12 weeks prior to study entry.
- 4.1.5 Peak plasma HIV-1 RNA level before initiation of HAART > 1000 copies/mL.
- 4.1.6 CD4 cell count > 300 cells/mm^3 within the 12 weeks prior to study entry.
- 4.1.7 Nadir (lowest) CD4+ cell count > 250 cells/mm^3 at any time prior to study entry.
- 4.1.8 The following laboratory values, obtained within 30 days prior to study entry:
  - Absolute neutrophil count (ANC)  $\geq 1000/\text{mm}^3$
  - Hemoglobin  $\geq 9.0$  g/dL
  - Platelet count  $\geq 50,000/\text{mm}^3$
  - Serum creatinine  $\leq$  upper limit of the laboratory normal range (ULN)
  - AST (SGOT), ALT (SGPT), and alkaline phosphatase  $\leq 2.5 \times \text{ULN}$
  - Total bilirubin  $\leq 2.5 \times \text{ULN}$

- Anti-nuclear antibody (ANA) titer of 1:40 or lower and negative for serum anti-double-stranded DNA antibody (anti-ds-DNA) test result at screening.

- 4.1.9 All women of reproductive potential (who have not reached menopause or undergone hysterectomy, oophorectomy, or tubal ligation) must have a negative urine  $\beta$ -HCG pregnancy test performed within 14 days prior to study entry.

Female study volunteers who are not of reproductive potential (who have reached menopause or undergone hysterectomy, oophorectomy, or tubal ligation) or whose male partner has undergone successful vasectomy with documented azoospermia or has documented azoospermia for any other reason, are eligible without requiring the use of contraception. Acceptable documentation of menopause, sterilization, and azoospermia is written or oral documentation communicated by clinician or clinician's staff of one of the following:

- Physician report/letter
- Operative report or other source documentation in the patient record
- Discharge summary
- Laboratory report of azoospermia (required for acceptable documentation of successful vasectomy)
- FSH measurement elevated into the menopausal range as established by the reporting laboratory.

- 4.1.10 All subjects must not participate in a conception process (e.g. active attempt to become pregnant or to impregnate, sperm donation, in vitro fertilization) and, if participating in sexual activity that could lead to pregnancy, the study volunteer/ partner must use two reliable methods of contraception simultaneously while receiving the protocol-specified vaccination(s) and for 3 months after the last vaccination.

A Combination of TWO of the following methods must be used:

- Condoms (male or female) with or without a spermicidal agent.
- Diaphragm or cervical cap with spermicide
- IUD
- Hormonal-based contraception

 Condoms are recommended because their appropriate use is the only contraception method effective for preventing HIV transmission.

 An IUD is an adequate method of birth control, but increases the risk of pelvic inflammatory disease.

4.1.11 Karnofsky performance score (Appendix II)  $\geq$  90 within 30 days prior to study entry.

4.1.12 Men and women age 18-50 years.

## 4.2 Exclusion Criteria

4.2.1 Viral load measurement  $>$  50 copies/mL within the last 12 weeks prior to study entry.

4.2.2 History of or evidence of active skin disease (atopic dermatitis, psoriasis, etc.), chronic autoimmune disease or any other significant active skin disease.

4.2.3 Treatment with topical corticosteroids in close proximity to the proposed vaccination sites within 2 weeks prior to study entry.

4.2.4 Excessive exposure to the sun (e.g., sunbathing, tanning bed) within 2 weeks prior to study entry.

4.2.5 Use of any local skin treatments to the targeted vaccination sites within 7 days prior to study entry.

4.2.6 History of diabetes and bleeding disorders.

4.2.7 Previous CDC category C event as defined in Appendix I.

4.2.8 Pregnancy or breast-feeding.

4.2.9 Use of immunomodulating therapy, including cyclosporin, IgG-containing products, interleukins, interferons, systemic glucocorticosteroids, or exposure to an experimental HIV vaccine within 6 months prior to study entry.

4.2.10 Receipt of any vaccine within 30 days prior to study entry.

4.2.11 Allergy/sensitivity to study vaccine products, including adhesives, will be excluded.

4.2.12 Active drug or alcohol use or dependence that, in the opinion of the investigator, would interfere with adherence to study requirements.

4.2.13 Serious illness until subject either completes therapy or is clinically stable on therapy, in the opinion of the site investigator, for at least 14 days prior to study entry.

4.2.14 Hepatitis B surface antigen and/or anti-hepatitis C positive.

#### 4.3 Study Enrollment Procedures

4.3.1 Prior to implementation of this protocol, the protocol and consent form must be approved by the local institutional ethics committee.

Once a candidate for study entry has been identified, details will be carefully discussed with the subject. The subject (or parent or legal guardian if the subject is under guardianship) will be asked to read and sign the consent form.

Only subjects who meet the eligibility criteria at both the screening and pre-entry visits will be enrolled. Cohorts will enroll serially. After all 3 subjects of a given cohort (#1 or #2) have received their study vaccine administrations, and have remained on study through at least the 14th day, if no subject in any cohort has experienced a Primary Safety endpoint (defined in section 9.2.1), then the study will dose escalate by opening enrollment of subjects into the next cohort.

## 5.0 STUDY TREATMENT

### 5.1 Regimens, Administration, and Duration

Study treatment is DermaVir.

5.1.1 Subjects who meet the inclusion criteria will be sequentially enrolled into each cohort:

- Cohort 1:
  - Three subjects will receive a single low-dose vaccination (0.1 mg DNA/subject, 0.8 mL total, administered over two skin sites of 80 cm^2 each, 0.4 mL/site) at study day 0.
- Cohort 2:
  - Three subjects will receive a medium-dose vaccination (0.4 mg DNA/subject, 3.2 mL total, administered over four skin sites of 80 cm^2 each, 0.8 mL/site) at study day 0.
- Cohort 3:
  - Three subjects will receive a high-dose vaccination (0.8 mg DNA/subject, 6.4 mL total, administered over eight skin sites of 80 cm^2 each, 0.8 mL/site) at study day 0.

#### 5.1.2 LC0002 administration

- a) Materials for administration of LC002 will be supplied as a *DermaPrep* kit containing the following in a single pouch:
- One yellow exfoliating sponge
  - Four stripping tapes
  - Two skin patches (each for vaccination of an 80 cm^2 area)

In addition, the following materials are required:

- Disposable razors
  - Surgical markers
  - Alcohol swabs
  - 1-ml graduated syringes
  - Needles (21-gauge, 1 1/2" length)
- b) The final LC002 product should be kept at 4 °C after formulation and administered to the subject within 3 hours as follows (NOTE: Each step of the administration procedure must be documented on the CRF):

1. The subject should be seated comfortably on an examination table.
2. Identify the appropriate vaccination sites. Each site to be prepared corresponds to the size of one large DermaPrep patch.

|          | UPPER BACK    |              |             |              | VENTRAL UPPER THIGH |              |             |              |
|----------|---------------|--------------|-------------|--------------|---------------------|--------------|-------------|--------------|
|          | Right lateral | Right median | Left median | Left lateral | Right lateral       | Right median | Left median | Left lateral |
| Cohort 1 | 1             | -            | -           | -            | -                   | -            | 1           | -            |
| Cohort 2 | 1             | -            | -           | 1            | -                   | 1            | 1           | -            |
| Cohort 3 | 1             | 1            | 1           | 1            | 1                   | 1            | 1           | 1            |

**Note:** It is advisable to proceed by preparing one site at a time.

3. Without removing the backing, hold the skin patch (Cohort 1&2: 1 patch at each site; Cohort 3: 2 patches next to each other at each site) to the vaccination site and use a surgical marker to demarcate approximately 3cm from the outer corners of the patch. This will serve as a guide for preparing the skin for vaccination.
4. Carefully shave the entire marked skin site, plus the additional 3cm margin, using a disposable razor.
5. Disinfect the entire marked skin site, plus the additional 3cm margin, using alcohol swab and wait for the skin to dry. Repeat this procedure using a fresh alcohol swab.  
**Note:** It is important that this procedure is performed thoroughly as it is the first step in removing the oily layer normally found on the surface of the skin. In addition, it improves adherence of the patch to the skin and thereby reduces the risk of leakage after vaccine application.
6. Gently exfoliate the entire marked skin site by rubbing the yellow exfoliating sponge 50 times back and forth over the demarcated area, applying light pressure, but taking care not to break the skin (1 exfoliation is equal to 1 forward and backward rub).
7. Apply one stripping tape to the site and immediately strip off in one quick movement to remove residual cell matter from exfoliation on the skin surface. Repeat if necessary, using same piece of stripping tape, in order to cover whole area of the site.
8. Repeat taping procedure with second stripping tape at a 90° angle to the first taping.

9. Apply the one skin patch to the site.

The skin patch consists of 4 pieces: small white triangle backing (A), large white backing (B), semi-occlusive patch- thin, clear adhesive layer with a non-adhesive window, applied to skin (C), and a stabilizing layer - thick, clear adhesive layer, removed after application to skin (D).

[figure not shown]

- a) Holding onto (A), remove only the large backing (B).
  - b) Apply patch to the skin with (A) at the top. Ensure patch is placed within the demarcated and prepared skin site. Once adhered to the skin, a pocket is created between the patch and the skin surface. (A) remains attached to the patch, preventing the entire patch from sticking to the skin and allowing access to the pocket.
  - c) Firmly press and smooth the entire perimeter of patch to ensure complete contact with the skin. Repeat this procedure several times to prevent leaking once vaccine is applied to the pocket.
  - d) Remove the outer clear stabilizing layer (D), being careful not to detach the semi-occlusive patch (C) from the skin. Once the patch has been applied to the skin, (D) should start to peel away from the patch. Again firmly press and smooth edges and corners of the adhesive patch to ensure complete contact with the skin.
  - e) Run a flat hand from bottom to top of the patch to squeeze air out of pocket.
10. Using the 1ml-syringe and needle, draw the volume of DermaVir required for one site from the vial(s) provided:
- Cohort 1 - Low-dose vaccination: For each site, draw 0.4 ml of LC002 into syringe.
  - Cohort 2 - Medium-dose vaccination: For each site, draw 0.8 ml of LC002 from one vial into the syringe.
  - Cohort 3 - High-dose vaccination: For each site, draw 0.8 ml of LC002 from one vial into the syringe.

**Note:** Discard needle into a sharps container before proceeding to next step.

11. Carefully insert the 1ml-syringe (without needle), via the open corner formed by (A), into the pocket formed by the patch, so that the tip reaches the lower third of the pocket.
12. Slowly expel the DermaVir formulation into the pocket, and withdraw the syringe.
13. Remove (A) and close the pocket completely by sealing the upper edges of the patch, and check that all edges of the patch adhere well and are sealed.
14. Repeat this procedure for all remaining skin sites.  
**Note:** Use a new syringe and needle to draw DermaVir for each site.
15. The skin patch will be removed after 3 hours **at the clinical site** by the investigator. Patches may be discarded with general waste but must be kept safely out of reach of children or animals.  
**Note:** The investigator will evaluate local reactogenicity immediately after removal of the patch.
16. After removal of the skin patch, all treated sites are to be washed with clean water.

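### Section 5.1.2, step 3 has Cohort 3 staff mark two adjacent patches per site, although the rest of the protocol makes a site one 80 cm² patch; the dose is unaffected, but the skin prepared is not fixed (minor)

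*Protocol*

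**What the plan says.** Section 5.1.2 of the protocol gives the administration procedure step by step.

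- Step 2 defines the unit: "Each site to be prepared corresponds to the size of one large DermaPrep patch". Its table lists eight Cohort 3 positions (lateral and median, right and left, on the upper back and ventral upper thigh), with a 1 in each.
- Step 3 has staff hold the unopened patch to the skin and mark around it. Cohorts 1 and 2 use one patch per site, but the instruction continues: "Cohort 3: 2 patches next to each other at each site".
- Steps 4 to 6 act on that marking. Step 4: "Carefully shave the entire marked skin site, plus the additional 3cm margin". Step 5 disinfects the same area. Step 6 exfoliates by "rubbing the yellow exfoliating sponge 50 times back and forth over the demarcated area".
- Steps 7 and 8 use two stripping tapes per site.
- Step 9: "Apply the one skin patch to the site".
- Step 10: "High-dose vaccination: For each site, draw 0.8 ml of LC002 from one vial into the syringe".

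The regimen (Schema, sections 3.0 and 5.1.1) and the composition table in 5.2.3 give Cohort 3 eight sites of 80 cm² at 0.8 mL each, 6.4 mL and 0.8 mg DNA in all. Section 3.0 says the immunization is given once.

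Section 2.2 describes the highest dose cohort differently. It presents a swine regimen of 0.4 mg over four sites of 160 cm², given twice a week apart, as matching one vaccination series of that cohort. It also calls seven macaque vaccinations one more than that cohort is meant to receive.

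**The concern.** Step 3 uses the word site in a way that does not fit the other steps. In steps 2, 9 and 10 a site is one of eight 80 cm² areas carrying one patch. In step 3, for Cohort 3 only, a site holds two patches side by side. Because steps 4 to 6 prepare whatever step 3 marks, this wording decides how much skin is shaved, disinfected and exfoliated.

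Skin preparation is itself a source of local reactions: section 2.2 attributes the only side effects seen in the swine study to shaving and skin preparation. Section 6.3.6 has local reactions of every grade recorded. Table 1 in 7.1.1 grades ulceration, blistering or superinfection as 3, and under 9.2.1 a grade 3 event judged related is a primary endpoint event. An unintended difference in preparation confined to Cohort 3 would bear on how that cohort's local tolerability is read.

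**Working it through.** **1. Reproduce the Cohort 3 dose (5.2.3 and 5.1.1).** One formulation is 0.425 mL DNA + 1.275 mL dextrose + 1.70 mL PEIm mix = 3.40 mL. Two formulations make 6.8 mL. Concentration: 0.425 mg / 3.40 mL = 0.125 mg/mL. Given: 8 sites × 0.8 mL = 6.4 mL; 6.4 × 0.125 = 0.8 mg; 8 × 80 = 640 cm². All match the plan.

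**2. Could step 3 change the dose?** Sixteen patches at 0.8 mL would need 16 × 0.8 = 12.8 mL, against 6.8 mL made. Step 10 gives one 0.8 mL draw per site. The dose is fixed whatever step 3 marks.

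**3. Supplies.** A kit holds two patches and "Four stripping tapes", so two tapes per patch. Steps 7 and 8 use two tapes per site, so the kit implies one patch per site. Eight patches need four kits, which carry 4 × 4 = 16 tapes; eight sites use 8 × 2 = 16.

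**4. Patch footprint marked in Cohort 3.**

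| Reading | Calculation | Footprint |
|---|---|---|
| One patch at each of eight sites | 8 × 80 | 640 cm² |
| Step 3 literally, eight sites | 8 × 2 × 80 | 1280 cm² |
| Lateral and median marked as a pair in four body areas | 4 × 2 × 80 | 640 cm² |

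The 1280 cm² is a sum over sites and ignores any overlap between neighbours.

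**5. Including margins.** For a rectangular patch with side *w* along the line of the pair and margin *m*, the area prepared for two patches relative to one is (2*w* + 2*m*)/(*w* + 2*m*) = 1 + *w*/(*w* + 2*m*). This lies between 1 and 2, but neither input is settled. The text gives 80 cm² and no shape. Step 3 marks about 3 cm out and step 4 speaks of an additional 3 cm, so 3 or 6 cm could be meant. By assumption only:

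- Square patch (*w* = √80 = 8.94 cm), *m* = 3: 1 + 8.94/14.94 = 1.60
- Square patch, *m* = 6: 1 + 8.94/20.94 = 1.43
- 2:1 patch, *m* = 3: 1.51 (*w* = 6.32) to 1.68 (*w* = 12.65)
- 2:1 patch, *m* = 6: 1.35 to 1.51

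These also ignore overlap. They show the direction under the literal reading, not an estimate. With a square patch and a 3 cm margin, four shared-margin pairs total 4 × 23.89 × 14.94 = 1428 cm², against 8 × 14.94² = 1787 cm² for eight separately marked sites. Paired marking therefore adds no skin.

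**6. Which reading was meant?** In the step 2 table, Cohorts 1 and 2 never use the lateral and median positions of the same side and region. Cohort 3 uses both in all four body areas, which is the same split that step 3 makes. Section 2.2 describes four 160 cm² sites for the highest dose cohort: 4 × 160 = 640 cm², or two patches per area. Both point to paired marking. The word site does not carry that meaning through, however: four sites with one 0.8 mL draw each would be 3.2 mL, and 3.2 × 0.125 = 0.4 mg, not 0.8 mg.

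**7. Rubs.** If a pair is one demarcated area, step 6 gives it 50 rubs. If each patch position counts, it receives 2 × 50 = 100. The text does not choose. Sponge width and stroke direction are not stated, so no figure for intensity is offered.

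**8. Section 2.2.** Seven being one more than intended implies six vaccinations; section 3.0 gives one. Total area agrees (640 cm²). If the swine 0.4 mg is a total, which the text does not say outright, each application was half of Cohort 3's 0.8 mg: 0.4/640 = 0.000625 against 0.8/640 = 0.00125 mg/cm².

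**The case against.** The best defence is that step 3 is a sensible instruction loosely worded. Two patches can be held side by side over two adjacent one-patch positions, and trained staff who see the table, the kits and step 9 would probably do just that. This largely stands. It makes paired marking the likelier intent, and it means that simply deleting the Cohort 3 clause could remove a useful step and lead to neighbouring margins being prepared twice. It does not clear the text, because site changes meaning between steps and the number of rubs per pair stays open.

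A reader might infer several stronger things that the documents do not support:

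- **That Cohort 3 could receive sixteen patches or a double dose.** Steps 9 and 10 and the formulated volume rule this out.
- **That a definite percentage more skin is prepared.** That depends on an assumed shape and margin and on the literal reading; under paired marking there is no excess.
- **That escalation is compromised.** Under 4.3 and 9.1.3 the rule governs entry to Cohorts 2 and 3 only, and Cohort 3 is the last.
- **That this is what confounds dose with skin preparation.** Total prepared skin already rises by design with 2, 4 and 8 sites. The dose-response objective (1.2.1.4) concerns T-cell responses under patches whose area is unchanged.

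Step 6 also calls for light pressure without breaking the skin, the swine effects were mild and transient, and each administration step is documented on the CRF. The section 2.2 statements are background text that prints the actual animal regimens, so a careful reader can see the difference.

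**Conclusion.** The inconsistency is real and sits in operative text: step 3 conflicts with step 2, the site table, step 9, section 5.1.1 and the composition table on what a Cohort 3 site is. Step 10 only implies one patch. The wording is probably a remnant of a layout of four 160 cm² areas; that is an inference from the site table and section 2.2.

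The effect is limited to skin preparation in three subjects. Taken literally, the marked footprint is 1280 instead of 640 cm²; taken as paired marking, it is 640 cm². The excess including margins and the exfoliation intensity cannot be determined from the protocol. Expected harm is small. The point deserves correction because local reactions feed the primary endpoint and the remedy is a few words. Severity: minor. The section 2.2 statements are wrong for this protocol, but of background importance only.

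**What to change.** - **Step 3.** Replace the parenthesis with: *1 patch at each site in all cohorts; in Cohort 3 the adjacent lateral and median sites of a body area may be marked together by holding two patches side by side.*
- **Steps 6 to 8.** Add that 50 rubs and two stripping tapes are used per patch position, so that marking two positions together does not halve the preparation each receives.
- **Section 2.2.** Delete the statements that the swine dose and schedule reflect this protocol's highest dose cohort and that seven vaccinations is one more than intended for it. State that Cohort 3 receives 0.8 mg once over 640 cm², and whether the swine 0.4 mg was a total or per site.

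The cost is one parenthesis, one added sentence, two background corrections and a reminder to site staff before Cohort 3 opens. Dose, supplies, sample size, endpoint and escalation rule stay as they are.
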